### Objective

The study objective is to assess the clinical efficacy and safety of VH-90-D DiGA (DTx) for patients with vestibular vertigo.

Two hypotheses are proposed. First, DTx efficacy is hypothesized to show superiority compared to TAU. Attainment of this response would support the second hypothesis that the study can distinguish DTx efficacy from TAU.

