## Methods

### Study setting and design

This project is a prospective, randomized, group-controlled, single-blinded confirmatory clinical multi-center trial (German Vertigo Study, GEVE II study). Approved by the Ethics Committee of the German State of Baden-Württemberg Chamber of Physicians and Surgeons (F 2021–157) the study has been registered with the German National Registry of Clinical Studies (DRKS00028026). After oral information by a study physician, patients provide written informed consent to participate. In addition to the overall analysis, a separate analysis is planned for the results of each individual center. The scheme in Fig. 1 shows the overall design and clinical procedures of the study. During the follow-up, data acquisition will be performed. After 12 weeks, the study will be complete for an individual patient. If a patient is symptom-free prior to the completion of the study, he/she may discontinue therapy. These patients are not dropouts. After the last patient is out, a complete ITT (intention to treat) analysis will be performed. At T0, study physicians perform the initial clinical assessment in person and submit the results into the uniform online eCRF (electronic case report form, Magana Trial Manager, MaganaMed, Regensburg, Germany). All subsequent data are collected as ePROs using different sections of the same eCRF system. At the designated time points participants receive email links to the questionnaires, along with reminders.

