To minimize stratification bias, block randomization will be performed. A list of blocks will be created by researchers who are not involved in the performance of the clinical study. Allocation concealment will be achieved by envelope concealment as described by Doig and Simpson [30]. As additional security measures, the person creating the envelope will sign the back of the envelope when sealed. The envelope will be opened no earlier than at the end of the T0 visit to allow patients in the IG to be introduced into the app. Randomization will be performed at the end of the T0 visit by an independent research professional not involved in the trial.

Permanent patient blinding is not feasible. Patients will be blinded during the complete enrollment process until the randomization envelope is opened and patients do or do not receive the app. The researchers collecting the clinical study endpoints will be blinded throughout the study. For ethical and practical reasons, a separate external adverse event (AE) monitoring and app dysfunction committee will be established whose members will be assigned to AE patient care, hazard coping, and app support. In case of a serious adverse event, the German National Authority BfArM is informed indicating expectedness, seriousness, severity, and causality. They will not be blinded and will not collect endpoints. Except for medical emergencies, they will not have contact with patients’ prior endpoints retrieved by the blinded staff. They will contact patients in separate sessions.

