#### Internal validity

The randomization sequence will be established before the study participants are assigned to the different groups. At the time of study inclusion by the study physician, the randomization will still be secret. Thus, the selective selection of study participants into the different treatment groups is sufficiently counteracted.

Due to the lack of blinding of the patients to participation in the app intervention or physiotherapy, performance bias will be present to a certain degree, which has to be accepted due to the impracticable blinding. In the self-reported endpoints (patient-reported outcomes), there is no detection or observer bias. However, the functionality and AE surveys by separate, non-blinded external committee members are subject to detection bias. This is acceptable in that the functionality and AE survey is descriptive and do not include confirmative endpoints. Reporting bias will be minimized through pre-specification of the primary and secondary confirmative endpoints and statistical procedures including statistical handling of dropouts.

Attrition bias will be minimized by evaluating the ITT population using multiple imputation as a pre-specified procedure. In addition, the reasons for missing data and drop-outs will be collected and evaluated.

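### Adverse events are surveyed by unblinded committee members whose committee also supports the app; calling the survey descriptive does not excuse the conceded detection bias when safety is a stated objective

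*Protocol article*

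**What the plan says.** The Objective section reads: "The study objective is to assess the clinical efficacy and safety of VH-90-D DiGA (DTx) for patients with vestibular vertigo". The hypotheses that follow concern efficacy only ("First, DTx efficacy is hypothesized to show superiority compared to TAU"), and so do all seven ordered confirmatory tests. No formal test of AEs between arms is announced.

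Under Study interventions, the article gives ethical and practical grounds for setting up an outside body, apart from the endpoint staff, to deal with AEs and app faults. It describes this body as one "whose members will be assigned to AE patient care, hazard coping, and app support". Of its members it says: "They will not be blinded and will not collect endpoints".

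Internal validity concedes the consequence, "However, the functionality and AE surveys by separate, non-blinded external committee members are subject to detection bias", and continues: "This is acceptable in that the functionality and AE survey is descriptive and do not include confirmative endpoints".

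How AEs are collected is described in several places:
- Study setting and design says of everything after the T0 visit: "All subsequent data are collected as ePROs using different sections of the same eCRF system".
- Adverse event and harms reporting describes active surveillance by checklist with a free-text option, and points to Table 2.
- Adverse event reporting and harms, under Oversight and Monitoring, repeats this but points to Table 3.
- By their captions, Table 2 lists diagnostic procedures and Table 3 is the AE checklist. The content of Table 3 is not shown.

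**The concern.** That an analysis is descriptive means it carries no claim that needs control of the type I error. It does not make an event rate accurate. If the chance that an event is recorded differs by arm, the reported rates differ for that reason, with or without a p value. The plan gives its patient-reported efficacy endpoints a collection route that it regards as free of observer bias. For safety, the other half of the objective, it admits a weakness and waves it through.

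The committee's mix of duties sharpens this. App support exists only where there is an app, so the body that surveys AEs has a possible reason to be in touch with one arm that it lacks in the other. More contact could raise the app arm's count. An interest in the app, or treating a complaint as a device matter, could lower it. Either a difference or a reassuring equality in AE rates could therefore reflect recording as well as risk.

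**Working it through.** The plan states no figure on this point, so there is none to reproduce. The check has two parts.

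**1. The sections side by side**

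| Section | Who or what records AEs |
|---|---|
| Study setting and design | All data after T0 are patient-entered electronically; AEs are neither named nor excepted |
| Adverse event and harms reporting | Checklist plus free text; cites Table 2; recorder not named |
| Internal validity | AE surveys by non-blinded committee members |
| Adverse event reporting and harms | Checklist plus free text; cites Table 3; recorder not named |

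Read literally, the first and third rows name different recorders. They can be made to agree if patients complete the checklist and the committee follows up, but no section says so. Who records an AE, and which table is the instrument, is left unsettled.

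**2. How large unequal capture could be (illustration)**

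The only input from the document is 100 patients per arm (Sample size). The true AE risk *p*, equal in both arms, and the capture probabilities *c*₁ (app) and *c*₀ (control) are assumptions.

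- Observed risks: *a* = *p*·*c*₁ and *b* = *p*·*c*₀
- False difference: *a* − *b* = *p*(*c*₁ − *c*₀)
- 95% half-width: 1.96·√[*a*(1 − *a*)/100 + *b*(1 − *b*)/100]

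Worked case, *p* = 0.20 and capture 0.90 v 0.70: *a* = 0.18, *b* = 0.14, false difference 0.04. Half-width = 1.96·√(0.1476/100 + 0.1204/100) = 1.96 × 0.0518 = 0.101.

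False difference, with 95% half-width in brackets, in percentage points:

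| True risk | 95% v 85% | 90% v 70% | 100% v 50% |
|---|---|---|---|
| 10% | 1 (7.9) | 2 (7.5) | 5 (7.3) |
| 20% | 2 (10.6) | 4 (10.1) | 10 (9.8) |
| 30% | 3 (12.3) | 6 (11.8) | 15 (11.4) |

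With equal capture the false difference is 0. If capture is better in the control arm, each difference changes sign and the half-width stays the same.

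A moderate imbalance gives 1 to 6 points, less than the sampling error. Only the extreme imbalance, at true risks of 20% or more, matches or exceeds it. Unlike sampling error, the bias does not shrink with more patients and is not reflected in the interval.

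**The case against.** The strongest reply is that this is a disclosed limitation with a safeguard already in place. Surveillance is active and uses a fixed checklist, which limits the surveyor's discretion and the reliance on chance contacts. Nothing confines the checklist to the app arm. Tables 3 and 4 and Fig. 1, which may show who completes it and when, are not reproduced, so an identical schedule in both arms may already be the design. No formal AE comparison is planned. Blinding the surveyors would not cure reporting bias either, since patients know their treatment.

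Most of this stands, and it rules out three stronger readings that a reader might draw:
- **That the AE comparison cannot be interpreted.** Neither the size nor the direction of the bias is established, and moderate imbalance in the illustration stays within sampling error.
- **That controls have no comparable channel.** Study interventions has committee members contacting patients in separate sessions without limiting this to one arm, and Follow-up measures has investigators checking with participants remotely at T1 and T2. Only the app-support route is particular to one arm. Nor does the text say that each committee member performs every task.
- **That Study setting and design flatly contradicts Internal validity.** The former describes emailed questionnaires and does not mention AEs.

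What the reply does not rescue is the reason given. Disclosure and a checklist are mitigations; being descriptive is not one. The article relies on the latter.

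**Conclusion.** The point holds in a limited form. Safety is an objective, the AE surveyors are unblinded, their committee also supports the app, and the conceded detection bias is accepted on a ground that does not address it. The descriptive AE comparison is open to differential ascertainment of unknown size and direction and should be read with caution.

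The sizes above rest wholly on assumed risks and capture rates; they show scale and are not estimates for this trial. That app support leads to extra recording in the app arm is an inference, because contact frequency is not given. The confirmatory efficacy tests are not affected. This is a weakness of moderate weight with an inexpensive improvement available.

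**What to change.** 1. State that patients in both arms complete the Table 3 checklist and free text in the existing electronic system at T1, T2 and T3, with the same wording and timing. Make these solicited entries the main basis of the descriptive arm comparison.
2. Still report all AEs and serious AEs. Tabulate those that surfaced through app support or committee contact separately, by arm and source. Dropping them would lose events in patients who stop answering questionnaires.
3. In Internal validity, replace the statement that the detection bias is acceptable with a stated limitation.
4. Reconcile Study setting and design, Internal validity and the two AE sections on who records AEs, and correct the Table 2 reference.

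Trial status says the article was re-submitted after the study closed. If data collection is indeed over, item 1 cannot be introduced afterwards. The split by source should then be applied to the recorded data as far as the source can be identified, and items 3 and 4 remain possible.

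The cost is one form in a system already in use, some rewording and two AE tables instead of one, with no added staff. Reporting bias remains, because patients know their arm.

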#### Subgroup analyses

Subgroup analyses will be performed by age (< = / > 65), disease, disease type (permanent/attacks), disease duration, number of therapy/use days, falls/falling risk, responders, and disease severity/intensity/handicap.

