### Study interventions

The experimental arm (experimental group [EG]) will receive VH-90-D DiGA, Version 1.0.2 D (Digitale Gesundheitanwendung [Digital Health App], legal term according to the German Digital Care Law DVG [2019]. VH-90-D DiGA (Vertidisan®) is a Class I (MDR [18] Medical Device (UDI-DI 42700027834VH90-DN6) is Security Class B standalone software. The software is applied as a digital application to be used on smartphones or tablets. It is manufactured and provided by the manufacturer Digitineers GmbH & Co KG, Tübingen, Germany. Users tap on the device screen to control the application. They watch videos of exercise demonstrations by therapists and instructions by physicians and read instructions and information. The medical contents of the app are based on guidelines [19, 20], expert publications, established handbooks [21, 22], comparable recognized sources [8, 9, 23], or published studies [8, 9, 23–29].

Patients will be asked to use the app daily using the therapy plan provided in the DTx. Daily time consumption for app use is expected to be 10–25 min. During onboarding, a patient may indicate his/her diagnoses. According to the diagnosis, DTx provides 90 therapy days. Experimental patients are free to decide when and where to use the app. Thus, experimental patients choose their individually preferred application time.

The control group (control group [CG]) will receive physiotherapy. Control patients will receive a physiotherapy prescription and make appointments with a physiotherapist of their choice on their own. The physiotherapy consisted of the standard exercise therapy provided for dizziness by physiotherapists licensed to provide care for people with statutory health insurance in Germany and will not get further instructions regarding the trial.

According to the German “Heilmittelkatalog” (catalog of remedies), 6 sessions of 20 min each are possible per prescription, and up to 18 units are recommended as an indicative treatment volume.

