### Strategies to improve adherence to interventions

Program adherence will be determined by the number of exercise days actually performed. Because adherence to the study is observed by the app, dropouts will be recorded. Treatment compliance will be inferred from the adherence to the DTx program.

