### Secondary confirmatory endpoints

Group comparison of DHI change T0-T3 (ANCOVA), group comparison of CGI-I at week 12 (Wilcoxon-test), group comparison of CGI-S changes T0-T3 (ANCOVA), group comparison of DT changes T0-T3 (ANCOVA), group comparison of VSS-sf-AA changes T0-T3 (ANCOVA), group comparison of SF-36 changes T0-T3 (ANCOVA).

All tests of secondary endpoints (#2–7 above) will be 2-sided tests with *α* = 5%. For handling multiplicity, including alpha error avoidance, the above-listed endpoints will be tested in the above indicated a priori order as long as significance is reached; if significance is not reached for a certain variable, further listed variables can be tested only in a descriptive manner. This a priori rejecting procedure controls the multiple significance level of 5% in a strong sense for all primary and secondary endpoints.

All post hoc tests including subgroup analyses are planned as descriptive statistics with exploratory interpretation of p values and 95% CIs.

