#### Protocol non-adherence and missing data

Participants withdrawing from the study and reasons for withdrawal will be analyzed. Characteristics of participants and non-participants will be compared. Multiple imputation will be used to handle missing data. The primary analysis set is the FAS for ITT analysis. The secondary analysis set is the PP set. Drop-outs will be replaced with reference-based multiple imputation – “Jump to reference” [60]. This method is conservative in handling the attrition bias. Other methods will be applied as sensitivity analyses (e.g., LOCF, BOCF, and total mean replacement). The estimand will be the effect achievable in patients with an affinity for apps vs. TAU. Patients who are symptom-free prior to completion of the study are free to discontinue the therapy. These patients are not dropouts.

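### Two variables that arise after randomisation, therapy/use days and responder status, are listed as subgroups beside baseline factors without being marked as non-randomised

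*Protocol article*

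**What the plan says.** The Subgroup analyses section is a single sentence. Beside age, disease and disease type it names "disease duration, number of therapy/use days, falls/falling risk, responders, and disease severity/intensity/handicap". It gives no definition or cut-off for use days or for response, and it does not separate factors known at entry from those that arise later.

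Four other places bear on the point:

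- **Timing.** Under Study interventions: "Randomization will be performed at the end of the T0 visit". App use and response both come after that.
- **Source of the day count.** The article says how adherence is measured: "Program adherence will be determined by the number of exercise days actually performed. Because adherence to the study is observed by the app" (section Strategies to improve adherence to interventions). Under Study interventions: "According to the diagnosis, DTx provides 90 therapy days". The control treatment is counted in sessions that patients arrange themselves: "6 sessions of 20 min each are possible per prescription, and up to 18 units are recommended".
- **Early stopping.** Under Protocol non-adherence and missing data: "Patients who are symptom-free prior to completion of the study are free to discontinue the therapy". The study setting and design section says the same.
- **Status of the results.** Under Secondary confirmatory endpoints: "All post hoc tests including subgroup analyses are planned as descriptive statistics with exploratory interpretation of p values and 95% CIs".

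**The concern.** A subgroup estimate is a randomised comparison only if subgroup membership is settled before allocation or cannot be affected by it. Neither variable meets that condition.

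**Use days.** The count appears to come from the app, so controls would have no equivalent. Setting high users against all controls then selects patients in one arm and leaves the other unselected. Whatever drives use, such as motivation, prognosis or early recovery, is mixed with the treatment effect.

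**Responders.** Membership is decided by the outcome. Comparing arms among responders conditions on the result under study and hides much of any real difference, because part of the effect lies in how many patients become responders.

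At stake is the reading of the exploratory results. A use-day table placed beside valid baseline subgroups can be taken for evidence of dose-response, and a responder table can be taken for a treatment effect of a different size from the one the trial found.

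**Working it through.** The plan gives no figure for these analyses, so there is none to reproduce. The calculations below show how large the bias could be.

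**Inputs from the Sample size section**

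- Relevant effect: 5 points (15% of the 32-point range is 4.8).
- Effect said to be needed in reality, because imputation is conservative: 6 points.
- SD of the change: expected to be less than 12, so 12 is an upper bound.
- 100 patients per group.

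**Inputs assumed, not in the document**

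- Correlation r between use days and improvement: 0.2 to 0.4.
- Use days split at the median.
- Response: improvement of at least 5 points.
- Mean change: -5 in controls and, with a 6-point effect, -11 in the app arm.

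**Use days, no true effect**

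Under bivariate normality, the mean excess improvement of the upper half of users is r × SD × φ(0)/0.5, where φ(0)/0.5 = 0.3989/0.5 = 0.798.

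| r | SD | Spurious difference, high users against all controls |
|---|---|---|
| 0.2 | 12 | 0.2 × 12 × 0.798 = 1.9 |
| 0.3 | 12 | 0.3 × 12 × 0.798 = 2.9 |
| 0.4 | 12 | 0.4 × 12 × 0.798 = 3.8 |
| 0.3 | 8 | 0.3 × 8 × 0.798 = 1.9 |
| 0.3 | 6 | 0.3 × 6 × 0.798 = 1.4 |

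The bias is proportional to SD. It is zero at r = 0 and changes sign with r: at r = -0.3 and SD 12, high users would look 2.9 points worse than controls.

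A simulation of 3,000 trials (100 per arm, SD 12, ANCOVA with group and baseline) agrees. At r = 0.2 and 0.3, high users appear better than controls by 1.89 and 2.93 points, with nominal p below 0.05 in 15% and 29% of trials. Low users appear worse by 1.93 and 2.81 points. In all randomised patients the estimate stays within 0.06 of zero, with rejection of 5.0% to 5.6%.

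The sign of r is not known from the document. If motivated patients both exercise more and improve more, r is positive. If patients who become symptom-free stop early, the best improvers have few days, and r is pulled down or made negative.

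**Responders, true difference 6, SD 12**

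For a normal change with mean m, the mean given a change of -5 or lower is m - SD × φ(a)/Φ(a), with a = (-5 - m)/SD.

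- App arm, m = -11: a = 0.5, so -11 - 12 × 0.3521/0.6915 = -17.11.
- Control arm, m = -5: a = 0, so -5 - 12 × 0.3989/0.5 = -14.57.
- Difference: -17.11 - (-14.57) = -2.54, against a true -6. This is 1 - 2.54/6 = 58% too small.

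The simulation gives about 2.6 points among responders and 1.9 among non-responders. The missing part of the effect shows in the response rates, about 50% in controls and 69% in the app arm. With no true effect, the responder split shows no bias: estimates lie within 0.10 of zero and rejection is 5.1% to 6.0%.

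**The case against.** **No between-arm comparison is stated.** The section says only that analyses will be done by these variables. Use days could be described within the app arm, and responders could mean response rates by arm; both would be sound. This stands. A reader might infer that the plan commits to comparing arms within use-day and responder strata, but the text does not say so. What remains is that the two variables share one undifferentiated list with baseline factors, and that tests and confidence intervals are foreseen for subgroup analyses in general.

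**App arm only is an inference.** It follows from the app recording exercise days and from therapy days being the programme's own unit. The wording could also cover physiotherapy days. Even then the variable would arise after randomisation and would not be comparable between arms, with 90 programme days on one side and 6 sessions per prescription on the other.

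**The direction is not secure.** A reader might infer that use days must show a false benefit of the app. The early-stopping provision could reverse the sign, so the documents do not support that.

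**The analyses are exploratory.** This is true and it limits the consequence. But the label deals with multiplicity, not with selection. An interval centred on the wrong quantity stays there whatever it is called.

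**A condensed article leaves detail to the SAP.** Cut-offs, and the exact handling of the other subgroups, fairly belong there and are not criticised here. The choice of the two variables is different, because the article states it.

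**Conclusion.** The point holds in a limited form. Two post-randomisation variables, one of them a function of the outcome, are named as subgroups without being marked as non-randomised. Any comparison of the arms within them would be biased.

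The bias for use days could be of clinical size: 1.9 to 3.8 points, against a relevant effect of 5, if r is 0.2 to 0.4 and the SD reaches 12. It shrinks with the SD and reverses with a negative correlation. The bias for responders is attenuation, about 2.5 points instead of 6 under the assumed cut-off and arm means. It vanishes under a full null and so cannot by itself create a false claim for the app. These sizes rest on assumptions; that such comparisons are not randomised does not.

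A reader might go further and doubt the trial's main result. The documents give no ground for that. The primary test, the ordered secondary tests, their 5% level and the sample size do not depend on these subgroups.

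**What to change.** - Limit subgroup analyses of the treatment effect to variables fixed at T0, and take number of therapy/use days and responders off that list.
- Report use days as a description within the app arm, labelled as non-randomised. The label is needed there too: at r = 0.3 and SD 12, the upper and lower halves of users would differ by 2 × 2.87 = 5.7 points with no effect of use at all.
- Report response as an outcome: the proportion responding by arm, in all randomised patients.

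The cost is one or two sentences in the analysis plan. No new data, no change to the sample size and no change to the confirmatory tests are needed.
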